## Abstract

**Background:**

While homelessness among youth is a serious problem, there is little information about evidence-based interventions for homeless youth. In cooperation with professionals and youths, [name] (2012) developed Houvast (Dutch for ‘grip’): a strengths based method grounded in scientific and practice evidence. The main aim of Houvast is to improve the quality of life of homeless youths by focusing on their strengths, thus stimulating their capacity for autonomy and self-reliance.

**Method/Design:**

The effectiveness and fidelity of Houvast will be tested in ten Dutch services for homeless youth which are randomly allocated to an intervention group (*n* = 5), or a control group which provides care as usual (*n* = 5). Measurements of both objective and subjective quality of life and secondary outcomes (mental and physical health, substance use, coping, resilience, psychological needs, care needs, working relationship with the professional and attainment of personal goals) will be conducted among homeless youths (*n* = 251). Youths in both groups will be interviewed by means of a structured interview at baseline, at time of ending care or after having received care for six months (T1) and at nine months after baseline (T2). Model fidelity will be tested around T1.

**Discussion:**

This study is unique as it includes a large number of homeless youths who are followed for a period of nine months, and because it focuses on a strengths based approach. If the Houvast method proves to be effective in improving quality of life it will be the first evidence-based intervention for homeless youth.

**Trail registration:**

Netherlands Trail Register (NTR):NTR3254

## Background

Homelessness among youth is a serious problem in many countries. Although, some researchers estimate that as many as 50000 homeless adolescents are, sleeping rough, in the United States, there is no accurate picture of the number of homeless youths in the U.S. [1]. For most European countries this information is lacking as well. Although the estimation of homeless youths in the Netherlands varies widely, the minimum estimate of sheltered youths and street youths is 9000 [2]; this is 0,9% of the total population of youth between 18 and 23 years old [3].

Research has consistently shown that homeless youth, a highly vulnerable and heterogeneous population, suffer from a wide range of problems. Some youths are physically, emotionally and/or sexually abused, many have experienced family conflicts and have parents who were unwilling or unable to care for them [4,5]. Many youths have become dependent on services for homeless youth, have lived on the streets, or have found temporarily shelter with friends. The majority of homeless youths experience a low quality of life and lack the personal and social resources to hold their own successfully [6]. On average, they have little money to spend because of lack of income or high debts, a low level of education, are struggling to maintain a daily routine, and frequently, experience limited support of their social network which mostly consists of other homeless people [6-8]. Homeless youths report health problems, such as headaches and skin- and teeth problems [6]. Most studies found heightened rates of substance abuse [9]. The percentage of daily cannabis use among homeless youths in the Netherlands varies between 30% - 63% [8,10-12]. Also mental problems, such as depression, anxiety and psychological distress are common [9,13,14]. Many have lost trust in professionals and services [15]. Approximately 12-25% of homeless adolescents suffer from an intellectual disability [9,16].

Despite all the hardships homeless youths have suffered in their young lives and all the problems they are confronted with, some show remarkable resilience and many are able to make a successful transition into adulthood. Their own resources and personal power, and their ability to learn from their difficult experiences, are crucial factors in this success [17,18]. Both internal factors (e.g. self-esteem and self-efficacy, intelligence, perseverance) and external factors (e.g. affectional ties that encourage trust and autonomy) can contribute to the development of resilience [19]. Especially high self-esteem and self-efficacy are essential and seem to be acquired through supportive relationships [18]. Research on resilient children has shown that if a parent is incapable or unavailable to raise a child, other significant people can play an important role whether they are grandparents, siblings, care-providers or school teachers. In many situations it makes more sense to strengthen informal ties than to introduce additional layers of professionals [18-20].

To date, there are only few studies reporting on interventions among homeless youth: in a recent review on effective interventions only eleven published studies were found [21]. When looking at the interventions that are available for homeless youth in services for ambulant or residential care, the most promising are cognitive-behavioural interventions [21-24].

Yet, even though there is little information available on evidence-based interventions, some studies mention a supportive working relationship between professionals and youths as a crucial element in an effective intervention, [4,25-28]. Preliminary but promising results regarding higher levels of social connectedness and a trend towards decreased feelings of hopelessness were found in a study about the evaluation of the impact of a relationship-based intervention among homeless youth [29]. In the Netherlands in general, a variety of methods or approaches are being used in services for homeless youth, but there is no evidence for the effectiveness of these methods. Furthermore, research has shown that the available interventions hardly fulfill the needs of homeless youths [16]. When looking at the specific needs of homeless youths, they primarily wish to be taken seriously, to receive care from professionals who are committed, honest, authentic and flexible, and to have easy access to practical support and care [8,15,16,25].

In cooperation with professionals and homeless youths themselves, [name] [30] developed a strengths based method, named: Houvast (Dutch for 'grip'). During the development of Houvast different activities were conducted to determine which elements are crucial for an intervention for homeless youth. Interviews were held with workers who homeless adolescents considered to be ‘effective’. In addition, focus groups with homeless youths were held as consultation of the target population is important in the process of developing an effective method [4]. Furthermore, a review [21] gave insight into available interventions and their scientific evidence.

Both scientific and practical evidence underlined the importance of a strengths based method. Houvast has been derived from a strengths based model that was originally developed for people with a psychiatric disability [31]. Currently, this model is being used with different subgroups of clients. Among abused women in Taiwan the strengths model contributes to a significant decrease in depression, a better life satisfaction and recovery from a sense of self [32]. Furthermore, a strengths based approach among persons with mental illness shows a positive association with number of hospitalizations, quality of life, social functioning and social support [33].

The main aim of Houvast is to improve the quality of life of homeless youths by focusing on their strengths and stimulating their capacity for autonomy and self-reliance. The fundamental assumption of the strengths perspective is that all people have strengths, talents and goals and that all environments consist of resources, people and opportunities. The strengths model emphasizes that the capacity for growth and recovery is an innate ability of human beings. Thus, even homeless youths who have experienced major live events can initiate change through exploring their inherent strengths and aspirations. The focus is on individual strengths rather than on problems and deficits. Young homeless people are their own director of the helping process and the working relationship is primary and essential for developing autonomy and self-reliance. The primary setting for work is the community which can be viewed as an oasis of recourses [30,34].

The present study aims to examine the effectiveness of Houvast in Dutch services for homeless youth and also to assess the fidelity of this strengths model. Studies that used fidelity scales have found better outcomes when services adhere closely to a model with specified critical components [35-37].

The research questions of the present study are:

1. Is Houvast more effective than care as usual in improving the quality of life among homeless youths?

2. Is Houvast more effective compared to care as usual regarding recovery in terms of mental and physical health, substance use, coping, resilience, psychological needs, care needs, working relationship with the professionals and attainment of personal goals?

3. To what degree is there consensus, between professionals and youths, on the degree of satisfaction with their working relationship?

4. What is the fidelity of the strengths based method and is there a positive association with the effectiveness of Houvast?

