## Methods

### Study design

The effectiveness and fidelity of Houvast are investigated by means of a quasi-experimental research design with two groups and one baseline and two follow-up measurements (Figure 1). Both the intervention group and the control group (‘care as usual’) consist of Dutch services for homeless youth which deliver ambulatory and/or residential care. The services are randomly allocated to the intervention (*n* = 5) or control group (*n* = 5). Stratified randomization is used to ensure that services which deliver ambulant and/or residential care are equally distributed among each group. Randomization of homeless youths was not feasible since entire teams were trained prior to the baseline measurement in the strengths based method. Hence, a quasi-experimental research design is the best feasible design.

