### Data collection

Measurements of primary and secondary outcomes are conducted among youths within the intervention group (*n* = 123) and the control group (*n* = 128) by means of three structured interviews. The first interview (T0) is conducted as soon as possible but within two weeks after the start of ambulant or residential care. Since the average duration of care delivered to homeless youths is three to six months, they are interviewed for a second time (T1) when services end care or when they have received care for a period of six months consecutively. The final follow-up interview (T2) takes place nine months after the first interview. In addition, professionals fill out an electronic questionnaire around T1 to obtain information about their perspective on the working relationship and the quality of life of a particular youth they provide care to. Based on the average number of homeless youths entering the participating services per year, the total period of the data collection is expected to be one year and nine months.

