### Care as usual

Youths in the control group receive care as usual. To get insight into care as usual, professionals fill in a questionnaire about education, years of working experience and the caseload. In addition, the contact person of each service in the control group answers general questions about the average intensity of care, coaching and the actual approach or method used.

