### Model fidelity

To assess the model fidelity of the Houvast intervention, different assessments are conducted. During a one-day audit by two trained researchers to the service, the following activities are carried out: an interview with the team manager, an interview with the supervisor (in case a supervisor is established), a focus group with homeless youths, a file analysis, and an observation of a strengths based group supervision. Professionals, the supervisor and the team manager all fill out a questionnaire on the implementation of Houvast (e.g. questions about caseload, tasks and activities, use of strengths assessment and recovery plan) before the audit takes place.

Model fidelity is assessed with the fidelity scale of the strength based method. The fidelity scale consists of ten indicators: 1) case manager responsibilities; 2) caseload ratios; 3) supervisor to staff ratio and supervisor; 4) group supervision; 5) strengths assessment; 6) integration of strengths assessment; 7) personal recovery plan; 8) community contact; 9) naturally occurring resources; and 10) hope-inducing behaviours [31,35]. The scale consists of three subscales: structure, supervision/supervisor and clinical/service. Each indicator is rated on a 1 to 5 scale after gathering information from multiple sources. A total fidelity score is obtained by averaging the scores on the ten indicators. Each service receives an extensive report with specific recommendations on how to improve their model fidelity.

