### Analyses

1) Differences in baseline characteristics (age, gender, education, nationality and ethnicity) between the intervention and control group will be checked by using Chi-square tests, Student’s t-tests and ANOVA's.

2) To examine if the Houvast method proves to be effective or not and to examine additional factors associated with quality of life of homeless youths, a two-level multilevel regression analysis will be used. Since data is clustered – youths are ‘nested’ in services – the analysis will be adjusted for the cluster effect at ‘service’ level. Analyses will be adjusted for potential confounders, such as gender, age, ethnicity, intellectual disability, duration of homelessness and model fidelity.

3) To assess the degree of consensus on the working relationship satisfaction between professionals and youths, a one-with-many design with multilevel analysis will be used. This design addresses the problems associated with non-independence and it accounts for interdependence between professionals and youths.

4) Regarding the fidelity assessment of the strengths based method of each service, all sources (e.g. questionnaires, interviews, observations) will be analysed and by averaging the scores on ten indicators a total score on a 5-point scale will be obtained, whereby a score of 4 reflects a sufficient model fidelity. The total score will also be used as a covariate when examining the effectiveness of Houvast.

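### The fidelity–effectiveness half of research question 4 rests on five service scores, and no comparable practice measure is described for control services

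*Protocol article*

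**What the plan says.** The fourth research question (Background) has two parts: "What is the fidelity of the strengths based method and is there a positive association with the effectiveness of Houvast".

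**Houvast services.** Study design allocates ten services at random, five to each arm. The Model fidelity section opens "To assess the model fidelity of the Houvast intervention, different assessments are conducted" and describes a one-day audit with interviews, a youth focus group, a file analysis and an observed group supervision. Before the audit, professionals, the supervisor and the team manager complete a questionnaire whose topics include caseload, tasks and use of the two main tools. Ten indicators are rated from 1 to 5, and "A total fidelity score is obtained by averaging the scores on the ten indicators". The Abstract places this measurement around T1.

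**Analysis.** Analyses, item 4, repeats that "by averaging the scores on ten indicators a total score on a 5-point scale will be obtained". The same item fixes a threshold ("whereby a score of 4 reflects a sufficient model fidelity") and makes the total a covariate when effectiveness is examined. Item 2 lists model fidelity among the confounders for which the two-level model is adjusted. No separate analysis of fidelity against outcome within the Houvast arm is described.

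**Control services.** Under Care as usual, professionals report education, experience and caseload, and one contact person per service "answers general questions about the average intensity of care, coaching and the actual approach or method used".

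**Both arms.** Under Data collection, "professionals fill out an electronic questionnaire around T1" about a particular youth. It covers the working relationship and quality of life, and no restriction to one arm is stated.

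**The concern.** Two things the study wants to learn depend on measuring what was delivered.

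The first is whether better delivery goes with better outcome. Fidelity takes one value per service, so the number of independent observations is the number of scored services, not the number of youths. The ten indicators and three subscales beneath the average add no services. The model into which the score is placed compares arms; it does not relate fidelity to outcome among services that deliver Houvast.

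The second is how to read a small or null effect. It could mean that the method does not work, that it was poorly delivered, or that control services worked in much the same way. The audit speaks to poor delivery. Similar working in controls would need a like-for-like measure in both arms, and none is described. Some overlap is conceivable: control services also joined a Houvast study voluntarily, and their teams had a one-hour presentation about it (Selection and inclusion criteria; Procedure).

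**Working it through.** **1. The plan's own figure.** The article gives no power figure for the fidelity association. Its main calculation reproduces: difference 0.74, SD 1.48, 80% power, two-sided 5% gives 2 × (1.960 + 0.842)² × (1.48/0.74)² = 62.8, so 63 per group, as stated under Sample size and power calculation.

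**2. Smallest significant correlation.** With k = 5 Houvast services there are k − 2 = 3 degrees of freedom, and r = t / √(t² + 3).
- Two-sided 5%: t = 3.182, so r = 3.182 / √(10.125 + 3) = 0.878.
- One-sided 5%, which fits a question about a positive association: t = 2.353, so r = 2.353 / √(5.537 + 3) = 0.805.

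**3. Power with five services** (simulation, 200,000 bivariate normal samples):

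| True r | Two-sided | One-sided |
|---|---|---|
| 0.5 | 13% | 22% |
| 0.7 | 27% | 42% |
| 0.8 | 42% | 59% |
| 0.9 | 67% | 81% |

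**4. How large could the true correlation be?** Take the article's ICC of 0.05 and 178/10 = 17.8 youths per service at T1. Suppose fidelity explained all the between-service variance. The correlation of fidelity with service means would then be √[0.05 / (0.05 + 0.95/17.8)] = √(0.05/0.1034) = 0.70. That best case gives about 26% power two-sided and 41% one-sided. Over an assumed range of 12.5 to 25 youths per service, the correlation is 0.63 to 0.75 and two-sided power 21% to 34%.

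**5. Precision of an estimate.** An observed r of 0.8 with five services, by Fisher's z: 1.099 ± 1.96/√2 = −0.287 to 2.485, so a 95% interval of −0.28 to 0.99.

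**6. The covariate route.** The score is taken around T1, after allocation, and describes delivery of the intervention.
- If controls are not scored, it is undefined for half the services.
- If they are scored, it largely repeats the arm. With illustrative, assumed scores of 3.4, 3.7, 4.0, 4.2, 4.5 (Houvast) and 1.3, 1.6, 1.8, 2.0, 2.3 (control), its correlation with arm is 0.948 and the variance inflation factor is 1/(1 − 0.948²), about 10. The adjusted arm effect would then be a contrast at equal fidelity, where these assumed scores have no overlap.

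Scoring all ten services would lower the two-sided critical |r| to 0.632, but that correlation would mostly carry the difference between arms.

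**7. Reduced contrast, as illustration only.** If an assumed 10% to 20% of control youths received equivalent work, the planned 0.74 would become 0.74 × 0.9 = 0.67 to 0.74 × 0.8 = 0.59. The article gives no basis for any particular share.

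**The case against.** Much can be said for the plan, and several stronger readings fail.

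- **A reader might infer that research question 4 cannot be answered at all.** It can in part. The level of fidelity comes from a multi-source audit, including files and questionnaires that cover tool use, with a stated threshold. The association can be described; it cannot be tested with useful power.
- **A reader might infer that strengths-based work in control services would be invisible.** The contact person is asked about the approach or method in use, so an openly adopted one would show. What could not be quantified is partial or informal use.
- **That controls are not audited is itself an inference.** It is the natural reading of Model fidelity, but Analyses, item 4, refers to each service without naming an arm. If controls are scored, the collinearity problem replaces the missing-score problem.
- **A reader might infer that the Discussion intends to explain away a null result by poor implementation.** It only names this as a possible explanation and as the reason for the implementation effort.
- **Contamination may be small.** Whole services are allocated, whole Houvast teams are trained over several days, and control teams had one hour about the study. Strengths-based elements that already belonged to usual care are part of the comparator. These arguments stand against assuming much spill-over; they do not supply a measurement of contrast.

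A multilevel model on all youths does not remove the limit. More youths make the service means more precise but add no fidelity values, and step 4 already allows for the number of youths.

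**Conclusion.** The concern holds in a limited form. The association half of research question 4 rests on five scores and 3 degrees of freedom: it needs |r| above 0.88 two-sided (0.805 one-sided), with about 13% power at a true r of 0.5 and 27% at 0.7. Even if fidelity explained all between-service variance at the article's ICC, two-sided power would be about a quarter. Adjusting the two-arm model for fidelity does not answer the question and would distort the Houvast effect.

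For control services, no practice measure on the same footing as the fidelity items is described, so the degree of contrast between arms could not be quantified.

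This rests on three assumptions: the audit is confined to Houvast services, the service totals behave roughly as normal variables, and the ICC is 0.05. The randomised comparison survives if fidelity is left out of the model. What suffers is one stated research question and the reading of a null or small effect.

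**What to change.** 1. **Analysis.** State that the five service scores and their relation to outcome will be reported descriptively, within the Houvast arm, as exploratory. Remove fidelity from the two-arm effectiveness model and from its list of confounders. Keep the comparison with the threshold of 4. This costs nothing.
2. **Control practice.** Give control professionals the caseload, task and tool-use items of the existing implementation questionnaire, alongside the form they already complete, at the end of intake so that the items do not cue practice. Compare the arms on these items as the measure of separation.
3. **Optional.** Add a few neutrally worded delivery items to the professionals' existing T1 questionnaire in both arms: whether and when a strengths assessment and a written plan with the youth's own goals were made, the number of contacts, and the share outside the service. About 178/2 = 89 Houvast youths would contribute at T1. Any association among youths within a service is exploratory only, because it is confounded by engagement and by length of care (T1 falls at the end of care or at six months).

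The cost is a few minutes per professional, with no extra visits or staff. Self-report may overstate delivery, and repeated T1 items carry a small risk of prompting the practice in control services.
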